^f^ HIV testing for children younger than 24 months will be performed via PCR and repeated with Rapid Diagnostic Test (RDT) at end of study to adhere to national guidelines; HIV RDT will be performed at screening for participants 24 months and older and will not be repeated at end of study.

^g^ HIV and measles serum IgM/IgG results must be reviewed for eligibility confirmation prior to Day 14.

^h^ Blood will be collected for hemoglobin test via finger and/or heel stick. Hemoglobin and urine pregnancy rapid test results must be reviewed prior to venous blood sample collection.

^i^ Females of child-bearing potential must have a negative pregnancy test prior to enrollment and each rabies vaccine administration.

^j^ Optional photography of the skin rash and/or Koplik spots for documenting the phenotype of the signs of the potential cases.

^k^ Measles vaccination to be offered to ineligible participants and administered to eligible control participants (through the study or referral to Ministry of Health vaccination program) if serum and PCR measles IgG and IgM are both negative.

^l^ 5 mL is the maximum volume that will be obtained at each blood draw.

^m^ Vitamin A will be administered at D0 to all participants with clinical measles per WHO guidelines: 2 oral doses of 200,000 IU given 24 hours apart. The first dose will be administered at the study site and the second will be provided to the parent to be administered 24 hours later.

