### Known Potential Benefits

Control participants with negative serum measles IgM and IgG will be provided measles vaccination by the study team or through the national immunization program. All participants with suspected measles will be provided Vitamin A by the study team according to WHO guidelines.[[30](#_ENREF_30)] This treatment replenishes deficient vitamin A levels during measles that occur even in well-nourished children and can help prevent eye damage and blindness as well as reduce mortality.[[30](#_ENREF_30), [31](#_ENREF_31)]

All participants will receive PrEP with Verorab (inactivated rabies vaccine) as part of the study. The WHO rabies PrEP recommendation includes a 2-dose option.[[32](#_ENREF_32)] Because the Sanofi Verorab rabies vaccine package leaflet [[33](#_ENREF_33)] has not yet been updated to include the 2-dose PrEP option and 3 doses is the current approved regimen in each of the proposed study countries, a 3-dose PrEP regimen will be used.

Rabies is estimated to cause 59,000 human deaths annually, and this number is thought to be a gross underestimate of the true burden of this disease. The highest mortality is in Africa with an estimated 21,476 deaths due to dog-mediated rabies each year.[[34](#_ENREF_34), [35](#_ENREF_35)] Because rabies is endemic in the regions where the study will be conducted, provision of rabies PrEP is a benefit to study participation. In the event there is a potential rabies exposure that occurs during the study, participants will be provided with post-exposure prophylaxis (PEP) with HRIG and rabies vaccine.

[figure not shown]

Death rates per capita (per 100 000 population) for dog-mediated rabies. Source :

<https://www.who.int/teams/control-of-neglected-tropical-diseases/rabies/epidemiology-and-burden>

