Participants will undergo blood collection for screening and research testing at Day 0, between Days 7 and10 (optional, if Day 0 measles PCR and IgM are negative or equivocal in a child that presents with signs and symptoms consistent with measles), Day 14, Week 13, and Week 52. An upper respiratory specimen for MeV PCR will be collected at Day 0. Urine will be collected from females of reproductive potential to check for pregnancy at study visits with rabies vaccination or research blood collection. Hemoglobin levels will be checked at each study visit prior to research blood collection. Research samples will be tested for humoral and cellular immune responses to rabies vaccination (used as a controlled immune system stimulus, see section 8) and other research testing as described below (section 7.3). In addition, targeted sequencing will be performed on the measles virus to identify specific genotype. Unbiased sequencing will be used to try to identify the etiology in participants who have signs and symptoms consistent with measles but who test negative for measles by PCR and IgM. Optional photographs will be taken of the rash and/or Koplik spots at Day 0 to characterize the phenotype of the participants who test positive or negative for measles. We will also collect information on healthcare system encounters throughout the study period to help determine the clinical impact of immune amnesia after measles infection.

Participants with acute measles at screening/enrollment will be provided vitamin A treatment if they have not previously received it as part of their treatment. The treatment will follow WHO guidelines: 2 doses of 200,000 IU to be taken orally, 24 hours apart. The first dose will be given at the screening/enrollment visit, and the second dose will be given to the parent/guardian to be given the following day. A participant who has a rabies exposure during study participation will be provided rabies PEP with HRIG and rabies vaccine according to standard practice and the approved Verorab dosing schedule and depending on PrEP status. Any participant who receives rabies PEP prior to the timepoint that they were scheduled (randomized) to receive rabies PrEP under this study will continue in the study for follow-up visits but not receive PrEP according to their assigned randomization schedule. Data from these participants will be analyzed as described in Section [8.3](#_Population_for_Analysis).

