## Description of Study Procedures

Measles vaccination: Participants who enroll as controls and are found to have a negative measles IgM and IgG serology will be provided measles vaccination by the study team or referred to receive the measles vaccine through the national immunization program to ensure these participants are protected against measles and do not develop a natural MeV infection during the study period. Control participants who have evidence of immunity to measles at screening will not be vaccinated.

Pregnancy test: Urine pregnancy testing will be performed.

Medical history, vaccination history, and concomitant medications: Medical history, vaccination history, and concomitant medications will be reviewed at screening and updated at indicated study visits (see Table 1).

Rabies vaccination: A 3-dose series of Sanofi Verorab (inactivated rabies vaccine) will be given according to the manufacturer’s standard dosing instructions. Participants will be randomized to receive the series at an early (Week 8) or late (Week 47) timepoint (see Table 1 for specific dosing timepoints).

Physical examination: Physical exam will include measurements of height, weight, vital signs (temperature, heart rate, and respiratory rate) for all participants and anthropomorphic measurement (MUAC) in children 12 to 59 months as indicated in Table 1, Schedule of Activities. At Visit 0, the physical exam will include an assessment for clinical signs and symptoms suggestive of acute MeV infection (e.g., skin rash).

Upper respiratory specimen: OP/NP swabs will be collected for PCR testing to diagnose measles and for research evaluations (see Section 7.3).

Blood draw: Blood samples will be drawn via finger/heel stick and/or venipuncture according to standard site procedures for laboratory evaluations and storage. The amount of blood drawn for research purposes at each visit (no more than 5 mL) will be within the limits allowed for research participants in each country and will be specified in the sites’ SSAs. If additional research samples or testing will be performed at certain sites, the tests, timing of sample collection, type of sample, and amount of blood, if applicable, must be described in the SSA and MOP.

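### Table 1 footnote m gives vitamin A at Day 0 to every participant with clinical measles, while Section 4.1 withholds it from those already treated

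*Protocol*

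**What the plan says.** Vitamin A is mentioned as something the study gives in three places.

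- **Section 4.1, Overall Design.** A participant who has acute measles on entry is given vitamin A on one condition: "if they have not previously received it as part of their treatment". The regimen follows: "The treatment will follow WHO guidelines: 2 doses of 200,000 IU to be taken orally, 24 hours apart". The first dose is given at the screening/enrollment visit, and the second goes home with the parent or guardian.
- **Section 1.3, Table 1, footnote m.** "Vitamin A will be administered at D0 to all participants with clinical measles per WHO guidelines". The footnote gives the same two oral doses of 200,000 IU at the same 24-hour interval, and then the logistics: "The first dose will be administered at the study site and the second will be provided to the parent". It has no condition on prior treatment. The Table 1 row marks vitamin A at Visit 0 only.
- **Section 2.3.2, Known Potential Benefits.** "All participants with suspected measles will be provided Vitamin A by the study team according to WHO guidelines". This sentence gives no dose or visit and has no condition on prior treatment.

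Section 7 opens by sending the reader to Table 1 for the timing of assessments and procedures. Section 7.2, which describes the procedures one by one, has no vitamin A entry.

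**The concern.** Section 4.1 foresees that some children will arrive already treated for this illness, since its condition would otherwise have no purpose. For exactly those children, footnote m says the opposite. It is also more than a pointer to Section 4.1: it names who is treated, the dose, the interval, where the first dose is given and who gives the second. A member of staff could dose a child from the footnote alone and believe the protocol had been followed.

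Two things are at stake. A child may receive a second course that Section 4.1 did not intend, with some chance of the short-lived side effects that Section 2.3.1 lists, such as loose stools, headache, fever and vomiting, which that section calls rare. In addition, Section 9.8 defines a deviation as any departure from the approved protocol. Either action in an already treated child can then be called a deviation, and sites in different countries may act differently.

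**Working it through.** There is no statistical figure to reproduce. The check sets the two operative texts side by side and then does the dose arithmetic.

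**Comparison**

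| Element | Table 1, footnote m | Section 4.1 |
| --- | --- | --- |
| Who | All participants with clinical measles | Participants with acute measles |
| Prior-treatment condition | None | Only if not already given |
| Dose and interval | 2 × 200,000 IU, 24 h apart | 2 × 200,000 IU, 24 h apart |
| First dose | At the study site, Day 0 | At the screening/enrollment visit |
| Second dose | Given to the parent for the next day | Given to the parent/guardian for the next day |

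Dose, interval and logistics agree. The difference that changes what is given to an already treated child is the condition.

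**Inputs**

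- Dose per administration: 200,000 IU (Section 4.1 and footnote m).
- Doses per course: 2 (same sources).
- Level given for acute intoxication: more than 100 times 10,000 IU (Section 2.3.1).
- Dose received before Day 0: not stated. Assumed equal to the study course.

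**Study course**

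2 × 200,000 = 400,000 IU.

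**Given by the study to a child who already had a full course**

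- Footnote m: 400,000 IU.
- Section 4.1: 0 IU.
- Difference: 400,000 − 0 = 400,000 IU, one whole course.

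**Total if footnote m is followed**

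- Earlier course plus study course: 400,000 + 400,000 = 800,000 IU.
- Level in Section 2.3.1: 100 × 10,000 = 1,000,000 IU, to be exceeded.
- Margin: 1,000,000 − 800,000 = 200,000 IU below it.

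Adding the two courses treats them as if they were taken together, although the protocol does not say how long before Day 0 the earlier course would have been given.

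**Does any other text settle it?** Section 7 points to Table 1, which carries the unconditional footnote. Section 7.2 is silent on vitamin A. Section 4.1 leaves instructions for study procedures to a manual of procedures that is not at hand; its list of example topics does not name vitamin A. No sentence ranks the text of Section 4.1 above the table or the reverse.

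**The case against.** The strongest reply is that Section 4.1 is the more specific text. A condition stated once in the design section can be read as qualifying a table footnote that summarises it, and a careful site would read both. As a guide to what the authors meant, this is probably right, and the fix adopts it. It does not remove the conflict, because the footnote says all participants and reads as complete.

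A second reply is that footnote m refers to WHO guidelines, which may deal with prior treatment. Their content cannot be checked from the protocol. Section 4.1 also invokes those guidelines and still states the condition separately, so the reference cannot be relied on to supply it.

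A third is that the manual of procedures may resolve the matter on site. It may, but the approved protocol would still say two things.

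Part of the other side's case stands and limits the point:

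- A reader might count Section 2.3.2 as a third, rival dosing rule. It is a description of benefits with no dose or visit. The contradiction lies between footnote m and Section 4.1; Section 2.3.2 needs only to be kept consistent.
- A reader might go on to the child who has had one of the two doses and ask for a partial-course rule. The protocol does not mention that case, and a new dosing rule for it would be a clinical decision with no basis in the document.
- The three places say clinical, suspected and acute measles. The varying terms are untidy, but the documents do not show that they were meant to define different populations, and the point does not rest on them.

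**Conclusion.** The point holds as a contradictory dosing instruction, wrong as written and minor. For a participant already given vitamin A for this illness, footnote m calls for a further 400,000 IU and Section 4.1 for none, and the protocol does not say which applies.

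A reader might infer a toxicity hazard. The documents do not support that: on the assumption that the earlier course was the same as the study course, the total is 800,000 IU, below the level of more than 1,000,000 IU in Section 2.3.1. That section does not tie its figure to age or weight, so the comparison only shows that the protocol's own threshold is not reached. It is not a safety assessment for a small child. A reader might also infer an effect on the immune endpoints. The protocol says nothing that would support one, and no endpoint definition, sample size or analysis depends on this rule.

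How many children would be affected is not stated and cannot be derived. The reading of the texts needs no assumption; only the 800,000 IU total does.

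**What to change.** Add the Section 4.1 condition, "if they have not previously received it as part of their treatment", to footnote m of Table 1, and for consistency to the vitamin A sentence in Section 2.3.2. Section 4.1 can stay as it is.

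Prior receipt can be established from what is already collected at Day 0. Table 1 schedules medical history and concomitant medications at Visit 0, Section 7.2 states that "Medical history, vaccination history, and concomitant medications will be reviewed at screening and updated at indicated study visits", and Section 4.3 has supplements reported along with prescription and over-the-counter medicines. Staff need only look at that record before giving the first dose.

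The cost is a wording amendment in two places. Visits, procedures, sample size and analysis do not change.

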## Study Sites

Details regarding local investigators, study sites, and enrollment targets for each site are outlined in the site-specific appendix (SSA) for each country participating in the study.

## Concomitant Therapy

For this protocol, a prescription medication is defined as a medication that can be prescribed only by a properly authorized/licensed clinician. Medications to be reported in the Case Report Form (CRF) are concomitant prescription medications, over-the-counter medications, and supplements.

# STUDY POPULATION

## Inclusion Criteria

To be eligible to participate in this study, an individual must meet all of the following criteria:

1. Aged 1 to 15 years.
2. Ability of the participant’s legal or culturally acceptable representative to provide informed consent.
3. Ability to give assent, as appropriate.
4. Stated willingness of parent/guardian and participant as appropriate, to comply with all study procedures.
5. Willingness to receive rabies vaccine.
6. Meet the criteria for assignment to Group 1 or Group 2, as follows:
   1. Group 1, cases (acute MeV infection):

- Clinical signs and symptoms suggestive of acute MeV infection (Koplik spots or skin rash) AND
- Laboratory confirmed measles:
  - - - - Upper respiratory specimen (swab) PCR for measles positive.

OR

- - - - - Serum IgM for measles positive.
  1. Group 2, controls (no acute MeV infection):
- No clinical signs and symptoms suggestive of acute MeV infection (Koplik spots or skin rash) AND
  - - - Upper respiratory specimen (swab) PCR negative for MeV AND
      - Serum measles IgM negative AND
      - Serum measles IgG positive and previously vaccinated for measles (2^nd^ dose will be offered if appropriate). If serum measles IgG is negative, participant must be willing to be vaccinated regardless of prior measles vaccine history to meet this criterion.

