| Healthcare Utilization Questionnaire |  |  |  |  |  |  | X | X | X |  |  |  | X |
| Rabies vaccine |  |  |  | (X) | (X) | (X) |  |  |  | (X) | (X) | (X) |  |
| Research blood collection^l^ | X |  | X |  |  |  | X |  |  |  |  |  | X |
| Vitamin A | X^m^ |  |  |  |  |  |  |  |  |  |  |  |  |

Abbreviations: AE, adverse event; HIV, human immunodeficiency virus; Ig, immunoglobulin; MUAC, mid-upper arm circumference; NP, nasopharyngeal; OP, oropharyngeal; PCR, polymerase chain reaction.

(X) = Each participant will receive only one 3-dose series of rabies vaccine according to randomization to early group (vaccination at Visits 2, 3, and 4) or late group (vaccination at Visits 8, 9, and 10).

^a^ EARLY rabies vaccination: Only participants randomized to EARLY rabies vaccine attend Visits 2, 3, 4. Visit 2 occurs 8 weeks after Day 0; Visit 3 occurs 7 days after Visit 2; Visit 4 occurs 21 to 28 days after Visit 2 AND at least 14 days after Visit 3.

^b^ LATE rabies vaccination: Only participants randomized to LATE rabies vaccine attend Visits 8, 9, 10. Visit 8 occurs 47 weeks after Day 0; Visit 9 occurs 7 days after Visit 8; Visit 10 occurs 21 to 28 days after Visit 8 AND at least 14 days after Visit 9.

^c^ Day 0 is defined as the day screening occurs and the first research blood sample is collected. Inclusion/exclusion criteria evaluation for enrollment will be completed when PCR and measles IgG/IgM and HIV results are available, generally by Day 14. In cases where the clinical presentation is consistent with measles but the Day 0 tests (measles PCR and measles IgM) are negative or equivocal, an optional retest of the measles IgM can be done between Days 7 and 10. The guardian/parent will be informed of the need for a retest and asked to bring the child back to the clinic. Blood will be collected via finger stick for the retest and results will be available by Day 14. All potential participants (or guardian/parent) will be informed of eligibility status by a designated study staff by phone, if possible, prior to the Day 14 scheduled study visit or at the Day 14 scheduled study visit. Ineligible participants may be invited to the site to discuss test results and referral for measles vaccination if serum IgG and IgM are both negative.

^d^ Vital signs include temperature, heart rate, and respiratory rate; may be obtained prior to rabies vaccine administration, if clinically indicated.

^e^ MUAC in children 12 to 59 months old.

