# STUDY DESIGN

## Overall Design

This is a prospective, observational, longitudinal study to be conducted in select African regions to investigate the effects of MeV infection on pre-existing immunity, immune response to a known controlled immune stimulus (rabies vaccine), and susceptibility to infection to prevalent pathogens. Although children will receive the rabies vaccine as part of this study, we consider this an observational study rather than an interventional study. An interventional study tests an outcome of that intervention, e.g., efficacy or safety. The rabies vaccine is not used as a research intervention in this sense, i.e., we are not testing the efficacy or safety of the rabies vaccine, but rather using the vaccine as an immune stimulus to understand the effect of measles immune amnesia over time. In other words, the rabies vaccine is not the object of this investigation, but merely a means to allow assessment of the research objectives. Other vaccines could be used for this purpose, but rabies vaccine is convenient because there will not be pre-existing immunity to confound the results. The study is expected to take place in a subset of the NIAID Division of Clinical Research (DCR) Special Projects sites and any additional site(s) that may be identified. Specific study sites within each country will be in areas experiencing measles outbreaks.

We will enroll approximately 256 children aged 1-15 years into study Group 1 (acute MeV infection) or Group 2 (no acute measles infection). See section 5.1 for specific group criteria. In each group, approximately half of the enrolled participants will be ages 1-5 years and approximately half will be ages 6-15 years. Group 2 will be matched to Group 1 on gender and catchment area of study implementation.

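### Group 1 accepts IgM alone as laboratory confirmation regardless of recent measles vaccination, so a PCR-negative child with vaccine-induced IgM and a rash of another cause would be analysed as a measles case

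*Protocol*

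**What the plan says.** Section 5.1 defines Group 1 in two parts. The clinical part is "Clinical signs and symptoms suggestive of acute MeV infection (Koplik spots or skin rash) AND". The laboratory part is met by either of two results: "Upper respiratory specimen (swab) PCR for measles positive" or "Serum IgM for measles positive". Neither route refers to when the child was last vaccinated against measles.

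Group 2 requires "No clinical signs and symptoms suggestive of acute MeV infection (Koplik spots or skin rash) AND", a negative PCR and "Serum measles IgM negative AND". IgG-positive controls must have been vaccinated before, with no minimum time since vaccination.

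Other relevant provisions:
- Section 1.3, footnote c: for a measles-like presentation with negative or equivocal Day 0 tests, "an optional retest of the measles IgM can be done between Days 7 and 10".
- Section 4.1: "Specific study sites within each country will be in areas experiencing measles outbreaks", and "targeted sequencing will be performed on the measles virus to identify specific genotype". Genotyping serves an exploratory objective (section 3).
- Section 5.2, criterion 3, which concerns prior measles: its only mention of measles vaccination is to limit exclusion on immunologic evidence to children not vaccinated against measles.
- Section 7.1.2: vaccination history is collected at screening.
- Section 8.4: all enrolled participants are analysed. It has rules for a control who later gets measles and for a case diagnosed with measles again, but none for a case whose IgM may come from vaccination.

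**The concern.** Both primary objectives in section 3 concern the effect of measles virus infection, so Group 1 should consist of children with wild-type infection. IgM marks a recent response to measles antigen, and live measles vaccine can provoke that response as infection can. This is general immunology and is not stated in the protocol. The rash need not be measles either: section 3 gives, as a reason for one exploratory objective, that other pathogens may mimic the presentation.

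For a PCR-negative child, then, IgM-only entry cannot separate infection from recent vaccination plus another rash illness. Such a child can enter Group 1 but not Group 2, where both the rash and the IgM result disqualify. If these children show no amnesia and respond to rabies vaccine as controls do, they pull the panel contrast and the rabies contrast toward no difference. The power tables in section 8.2 make no allowance for this.

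**Working it through.** **1. Does any other rule close the route?** Take a PCR-negative child with a measles-suggestive rash of another cause and IgM from recent measles vaccination.
- 5.1, Group 1: clinical part met, laboratory part met by IgM. Eligible.
- 5.1, Group 2: fails on rash and on IgM.
- 5.2, criterion 3: the child has been vaccinated and has no history of measles, so it does not apply.
- 7.1.2: vaccination history is collected but used in no Group 1 criterion.
- 4.1 genotyping: a PCR-negative swab will seldom yield a measles sequence, and the result does not feed back into group assignment.
- 8.4: analysed as enrolled.

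Nothing closes it.

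**2. Inputs for the size (section 8.2).** Rabies titre: 0.85 SD, 30 per cohort, two-sided 0.05 (Table 2). Panel: 1.00 SD, 60 per arm within an age group, 0.025/1000 per tail (Table 3). Both tables target 90% power. The share f of cases affected is **not** in the documents; 2%, 5% and 10% are assumed for illustration.

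**3. Reproducing the plan's figures.** Two-sample t-test, df = 2n − 2, noncentrality = d × √(n/2). Solving for 90% power:
- Table 2, n = 20 / 30 / 40: 1.05 / 0.85 / 0.73, as stated.
- Table 3, n = 40 / 60 / 80: 1.26 / 1.01 / 0.87, against 1.26 / 1.00 / 0.86 stated.

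The tables are sound. At the stated differences:
- Rabies: df 58, critical t 2.00, noncentrality 0.85 × √15 = 3.29, power 90%.
- Panel: df 118, critical t 4.21, noncentrality 1.00 × √30 = 5.48, power 89%.

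**4. Dilution.** If a share f of cases behaves like controls, the expected difference is (1 − f) × d. With SD kept at 1:

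| f (assumed) | Rabies difference | Rabies power | Panel difference | Panel power | Sample-size factor 1/(1 − f)² |
|---|---|---|---|---|---|
| 0 | 0.850 | 90% | 1.00 | 89% | 1.00 |
| 2% | 0.833 | 89% | 0.98 | 87% | 1.04 |
| 5% | 0.808 | 87% | 0.95 | 83% | 1.11 |
| 10% | 0.765 | 83% | 0.90 | 76% | 1.23 |

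Allowing for the extra variance of a mixed case arm, f(1 − f)d², lowers the 10% row slightly further, to 82% and 73%.

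**The case against.** The strongest reply is that misclassification needs several things at once: recent measles vaccination, a presentation suggestive of measles, a negative PCR and a positive IgM. Any rash is not enough. Section 2.2 reports that 93% of suspected cases in one country's outbreak were confirmed, which suggests that most suspected children at such sites do have measles. It also ties the outbreaks to disrupted vaccination and does not mention vaccination campaigns at the sites. All this makes a small share plausible, and at 2% the loss is one to two points of power. It stands against any claim of a large effect, but it does not close the route.

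The panel figures use a Bonferroni correction over 1000 tests, which section 8.2 calls conservative. Section 8.5.2 plans a Westfall-Young procedure, expected to be more powerful. This stands: the panel powers are those of the planning calculation, not of the planned test.

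Four stronger readings are tempting, and the documents do not support them:
- *Recently vaccinated children without measles can enter only as cases.* A recently vaccinated child who is rash-free, PCR negative and IgM negative can be a control. An IgM-positive vaccinee without rash or Koplik spots enters neither group. Only the combination of vaccine IgM and a suggestive rash leads to Group 1 alone.
- *The IgM-negative rule for controls is itself a fault.* It keeps possible recent infection out of Group 2 and is reasonable.
- *Vaccination between Day 0 and the retest is a main source of error.* The child would have to be vaccinated elsewhere and become IgM positive by Days 7-10; the study's own measles vaccination is scheduled at Day 14. This is a remote case, worth covering only because the same sentence covers it.
- *No planned analysis would reveal the problem.* The SAP is not shown and may contain an analysis restricted to PCR-positive cases.

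**Conclusion.** The gap in the case definition is real: section 5.1 accepts IgM alone with no condition on recent measles vaccination, and no other section compensates. The bias is toward no difference in both primary contrasts, provided the affected children behave like controls. The size is unknown. Under assumed shares of 2% to 10%, power falls by about 1 to 7 points for rabies titre and about 2 to 13 points for the panel at the Bonferroni level. The loss is minor at the low end and material at 10%.

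The conclusion also rests on vaccine-induced IgM being possible, which the protocol does not state. An SAP could add a sensitivity analysis, but eligibility is fixed in the protocol, so the gap should be closed there. This is an inexpensive improvement that should be made, not a fatal flaw.

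**What to change.** **Section 5.1, Group 1.** State that a child vaccinated against measles within a pre-specified interval before the qualifying IgM sample (Day 0 or the Day 7-10 retest) qualifies by positive PCR and not by IgM alone. Take the interval from the IgM assay's documentation on positivity after vaccination.

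**Sections 1.3 and 7.1.2.** Record the date of the last measles vaccination at screening, and ask again at the retest.

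**Section 8.4.** State that a vaccine-strain sequence in such a child does not count as a case. This guards the PCR route only; it does nothing for the PCR-negative children at issue, for whom the eligibility sentence is the remedy.

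**Support.** Add a sensitivity analysis of both primary endpoints restricted to PCR-positive cases, unless the SAP already has it.

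**Cost.** A few sentences and one date field; PCR, IgM, vaccination history and sequencing are already planned. A few true PCR-negative cases vaccinated shortly before infection would be lost, a small burden on recruitment given the feasibility check in section 8.3. Restoring power by enrolment instead would take about 1.23 times the sample at an assumed 10% share and would leave the estimate itself diluted.
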